# Clinical prediction rules for persons diagnosed with an episode of severe mental illness for risk of violent crime and suicide – statistical analysis plan

## Study Summary

**Design:** Retrospective cohort study.

**Data:** Swedish databases linking hospital, crime, prescriptions, family relationships, housing and socio-economic status/deprivation data.

**Participants:** The study cohort is defined as individuals aged 15-65 with a diagnosis of any major psychosis (including bipolar disorder, schizophrenia, schizophrenic spectrum, other psychotic illness), obtained from hospital records that encompass both inpatient and outpatient visits, during the study period.

**Study period:** Psychiatric episodes ('diagnoses') that occurred between 1st January 2001 and 31st December 2008 will be used to develop the model: one episode per person, chosen at random. Data on most risk factors, including prior convictions and family history, are available for the lifespan of the individual, and are therefore not subject to the same 2001 start date for diagnosis. An exception is treatment history, which is available from 2005 onwards.

**Risk factors:** Include demographic characteristics (including gender, age, educational level, birth country), previous offending, drug and alcohol addiction, familial factors (parental and sibling illness, criminality and suicide), treatment history and a measure of deprivation (see Appendix for complete list).

**Primary outcomes:** Two outcomes are specified: (i) any violent crime within 12 months of diagnosis; (ii) suicide within 12 months of diagnosis.

**Outputs:** The main objective is to produce models that estimate the probability of events for the two primary outcomes, with appropriate measures of predictive accuracy.

These models will be used to obtain scoring systems for the calculation of risk to be used prospectively at time of diagnosis. As part of the study, we will investigate whether it is appropriate to assign the resulting probabilities to discrete categories, such as low/medium/high risk.

## Statistical Analysis

Statistical analysis will be based on logistic regression, adjusting for risk factors, in each of two scenarios:

- (i) Violent crime within 12 months, from time of diagnosis
- (ii) Suicide within 12 months, from time of diagnosis.

Here, 'diagnosis' refers to episodes of psychosis for which a diagnosis was recorded within the period 1st January 2001 to 31st December 2008. The terms 'diagnosis' and 'episode' are used interchangeably in this document.

The method of analysis will be the same in both scenarios, so for clarity the explanation below refers to scenario (i).

In each case, the follow-up period represented in the data-set lasts for at least 12 months after diagnosis, and so it is not necessary to consider the possibility of censoring when performing the analysis.

### Random selection of diagnoses

Given a starting data-set of all patients and all patient episodes (diagnoses) between 1/1/01 and 31/12/08, patient episodes will be selected at random as follows:

- Select at random, with equal probability, one inpatient or outpatient visit per patient.
- Note that some patients have more than one inpatient or outpatient visit on the same day, and some inpatient or outpatient visits comprise more than one diagnosis; only one inpatient or outpatient visit per day will be considered for random selection (if an inpatient visit and an outpatient visit are listed contemporaneously, the inpatient visit will be used).
- Extraneous episodes that are recorded as occurring within the period of an inpatient stay (because of recording errors or otherwise) will be identified in the data-set as having a date of episode that is earlier than lower-numbered episodes for the same individual; these will also be removed before the random selection step is made.
- If the inpatient or outpatient visit comprises a schizophrenia-spectrum diagnosis (with or without a bipolar diagnosis), this is considered as the diagnosis at time of selection; otherwise bipolar is the diagnosis at time of selection.
- For inpatient stays, the assumed date of diagnosis is the date the inpatient stay ends.
- The randomly selection of diagnoses defines the final data-set for analysis, i.e. there will be no subsequent resampling of diagnoses.

## **Adjustment for risk factors**

Risk factors will be considered in three groups, of decreasing levels of priority. The 'List of risk factor variables' table in the Appendix specifies the group to which each variable is assigned.

Group 1 consists of variables that will be included in the statistical model regardless of statistical significance. These include demographic characteristics that it is necessary to include to ensure the model has face validity, and other risk factors strongly suspected on the basis of previous research to be associated with the two outcome measures.

Group 2 consists of variables likely to show an association with outcomes but which are not required to be included to achieve face validity. This group includes measures of prescribed treatment, a categorical variable indicating the diagnosis of the individual and proxy measures of disease severity, such as whether the diagnosis occurred while the patient was an inpatient or an outpatient. The model will use a backwards stepwise selection procedure to determine whether to retain these variables in the model, with Group 1 variables always retained and Group 2 variables sequentially rejected in order of p-value until no group 2 variables remain that have p-values greater than 0.1 (Royston and Sauerbrei, 2008).

Group 3 consists of variables for which there is weaker prior evidence to suggest that they will be associated with outcomes. This group includes a deprivation measure, a measure of marital status, an income measure and several variables relating to parental outcomes or characteristics. The model will use a backwards stepwise procedure to determine whether to retain these variables, holding fixed any variables from Groups 1 and 2 that are already included. Group 3 variables will be retained only if they have p-values less than 0.1.

This strategy of risk factor adjustment recognises that the final model must demonstrate face validity, whilst simultaneously allowing the inclusion of additional risk factors if they show an association with outcome variables. The variables are considered in three groups in this way to recognise that a parsimonious model is preferable (i.e. easier to use in practice), provided that it has acceptable predictive ability.

The same set of candidate covariates will be used for both models (barring the few exceptions listed in Appendix 1).

## **Clustering by family**

It is likely that the data-set will exhibit clustering by family: sibling or parent-child relationships for which a diagnosis of major psychosis occurs for more than one member of

the same family. If this is the case, the model will include a single random effect term to take into account family membership.

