Once a 'final' model has been found using the steps outlined above, its internal validation will be assessed using bootstrapping to assess its predictive accuracy (Harrell et al., 1996). The bootstrapping step will use repeated resampling of families (rather than individuals – see section 'Clustering by family') in order to preserve within-family correlation. The performance of the model will also be assessed using the external validation sample. Predictive accuracy will be summarised using several summary measures, including the concordance index (Harrell et al., 1982), the Brier score (Brier, 1950) and the net reclassification index (Pencina et al., 2008). The proportions of predicted and observed events at different levels of predicted probability will be compared using a calibration plot.

If it is deemed appropriate to split the predicted probabilities into just two categories ('Low' and 'High'; see below), sensitivity, specificity and positive and negative predictive values will also be reported.

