## **Presentation of findings**

The main output of the model will be a predictive probability, indicating the probability of occurrence of the outcome of interest within 12 months. The estimated coefficients of individual risk factors will be examined with a view to: (i) simplifying the prediction rule in order to make it easier to use in practice, for example by using integer-valued coefficients (including possibly resetting Group 1 variables with extremely poor predictive power to have a coefficient of zero) or even by dichotomising numerical variables, provided this does not compromise its predictive accuracy; and (ii) justifying a categorisation of the predicted probability into risk categories (for example 'Low risk' (<5%), 'Medium risk' (5-10%) and 'High risk' (>10%)). The latter would also benefit from an assessment of the number and characteristics of individuals that fall into the proposed categories in the model development sample and the validation sample.

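### The SAP does not say how the family random effect enters a new patient's predicted risk; a score built from the coefficients alone would understate average risk below 50% whenever the estimated family variance is above zero

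*SAP*

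**What the plan says.** - **Model.** SAP, Statistical Analysis: "Statistical analysis will be based on logistic regression, adjusting for risk factors, in each of two scenarios".
- **Family term.** SAP, Clustering by family: "It is likely that the data-set will exhibit clustering by family". The section explains this as more than one member of a family having a diagnosis. Where that occurs, "the model will include a single random effect term to take into account family membership". The trigger is therefore the presence of related patients, not the size of the estimated variance.
- **Product.** SAP, Presentation of findings, defines what is to be delivered: "The main output of the model will be a predictive probability, indicating the probability of occurrence of the outcome of interest within 12 months". Simplification of the rule starts from the estimated risk-factor coefficients, possibly as integers. Cuts at 5% and 10% are given as an example.
- **Use.** SAP, Study Summary: "These models will be used to obtain scoring systems for the calculation of risk to be used prospectively at time of diagnosis".
- **Unknown inputs.** SAP, Generalisability, offers mean imputation as an example for missing covariates. It says nothing about the family effect.
- **Checks.** SAP, Validation and goodness of fit, plans the concordance index, Brier score, net reclassification index, a calibration plot and a geographic validation sample. For internal validation, "The bootstrapping step will use repeated resampling of families". No recalibration step is stated.

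**The concern.** In a logistic model with a random intercept, the fixed intercept and coefficients are conditional on the family effect. They describe risk within a family whose effect is known. A new patient's family effect is not known, so a rule is needed for turning the fitted model into that patient's probability. The SAP gives none.

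The SAP builds its score from the risk-factor coefficients, and such a score has no place for a family term. Arithmetically this sets the family effect to zero. Because the logit link is non-linear, the risk at a zero effect is the risk in the median family, not the mean risk over families with the same covariates. Below 50% the median-family risk is the lower of the two.

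The main output is an absolute probability, possibly cut into categories at low risks. A shortfall there would affect calibration and the Brier score, and would move patients near a cut into a lower category.

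**Working it through.** **Inputs.** From the SAP: the logit link, a single family random effect, an absolute-risk output, and example cuts at 5% and 10%. The SAP gives no family variance, event rate or cohort size, so it has no figure of its own to reproduce. Assumed: a normal family effect u with variance s², varied from 0.0625 to 1.0.

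**Formulas.**
- Score without a family term: p0 = expit(η), where η is the fixed part of the linear predictor.
- Average risk for the same covariates: p = E[expit(η + u)], u ~ N(0, s²), by 80-point Gauss-Hermite quadrature.
- For a given true average risk p, solve for η, then report p0 and the relative shortfall 1 − p0/p.
- Intra-family correlation on the latent scale: s²/(s² + 3.29).

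**One case in full.** With s² = 1.0 and p = 10%, the solution is η = −2.564. Then p0 = expit(−2.564) = 7.1%, and the shortfall is 1 − 7.15/10 = 29%.

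**Risk shown when the true average risk is 1%, 5% or 10%.**

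| Variance s² | Intra-family correlation | 1% shown as | 5% shown as | 10% shown as | Relative shortfall |
|---|---|---|---|---|---|
| 0.0625 | 0.02 | 0.97% | 4.87% | 9.78% | 2-3% |
| 0.1 | 0.03 | 0.95% | 4.79% | 9.65% | 4-5% |
| 0.25 | 0.07 | 0.89% | 4.5% | 9.2% | 8-11% |
| 0.5 | 0.13 | 0.79% | 4.1% | 8.4% | 16-21% |
| 1.0 | 0.23 | 0.62% | 3.3% | 7.1% | 29-38% |

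**Direction.** The gap is nil at 50% and reverses above it. At s² = 1.0 a true average of 70% is shown as 73.5%.

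**Ranking.** For a given s², p increases with η. Averaging over u therefore leaves the order of patients, and the concordance index from the same coefficients, unchanged.

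**Simulation check.** One data set was simulated for each true standard deviation s, with an assumed structure of 50,000 single-member families and 5,000 pairs. Each was fitted by maximum-likelihood random-intercept logistic regression.

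| True s | Estimated s | Observed risk | Mean prediction, u = 0 | Mean prediction, averaged over u |
|---|---|---|---|---|
| 0.5 | 0.0 | 3.10% | 3.10% | 3.10% |
| 1.0 | 1.0 | 3.91% | 2.70% | 3.91% |
| 1.5 | 1.35 | 5.76% | 3.18% | 5.76% |

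Averaging over the fitted family effect removes the gap. Where the variance was estimated as zero, there was no gap to remove.

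**The case against.** The strongest reply is that the faulty step is not written down. The SAP nowhere sets the family effect to zero, and a prediction averaged over the random effect is consistent with "The main output of the model will be a predictive probability". This stands. A reader might infer that the plan is miscalibrated by construction in every new patient, but the SAP does not support that. What it leaves open is the prediction step. The zero setting follows only if the coefficients are turned into a score without further processing, which is the most direct reading of Presentation of findings.

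The size is also uncertain. The relevant variance is what remains after the covariates, and Appendix 1 includes parental and sibling violent crime, parental drug or alcohol use, parental psychiatric hospitalisation and parental suicide. These may absorb part of the familial variation. A small variance cannot be ruled out, and at 0.1 a true 10% is shown as 9.65%, which hardly matters. This stands too.

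Two further inferences go beyond the document. One is that most patients will be the only family member in the data, so that the variance is weakly identified; this is plausible, but the SAP gives no family structure. The other is that estimated family effects will be used in the development sample and inflate apparent accuracy; no section proposes this.

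Finally, the calibration plot and the external validation sample could reveal a material shortfall. That is true, but the SAP states no correction to follow. The 5% and 10% cuts are only examples, so a shift between categories is an illustration, not a planned result.

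**Conclusion.** The concern holds as a gap in the prediction step. The SAP pairs a model whose coefficients are conditional on family with an output that must be an average risk for patients of unknown family effect, and it does not connect the two. Followed in the most direct way, it understates average risk below 50% whenever the estimated variance is above zero.

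The size depends on a variance the SAP does not give. It runs from negligible (2-3% relative at 0.06) to material (29-38% at 1.0) for true average risks of 1% to 10%, assuming a normal family effect. It does not arise if no related patients are present or the variance is estimated as zero. The damage is to calibration, the Brier score and risk categories, not to discrimination. The choice changes the reported probabilities and costs little to fix in advance, so it should be settled in the SAP.

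**What to change.** Adopt one of two options in Clustering by family, and refer to it in Presentation of findings and in Validation and goodness of fit.

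1. Fit ordinary (population-averaged) logistic regression. Use family-clustered standard errors for the selection p-values and keep the family bootstrap already planned. The coefficients then give average risk directly.
2. Keep the random effect, and state that predictions are integrated over its estimated distribution before the score is built or simplified.

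Under either option, compute the calibration plot, Brier score and any risk categories on those same predictions, in the development and validation samples alike.

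The cost is a change of SAP wording. Option 1 makes the model simpler; option 2 adds a small amount of computation.

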### **Competing risks**

A competing risk model, which might model jointly the probability of two or more events (such as violent crime and death), will not be used for the main analysis for two main reasons. Firstly, the outcome variable will be analysed as binary, and secondly, every individual in the data-set is followed up for at least twelve months after the initial time point. The main concern in failing to allow for competing risks (in this case, death) is inappropriately treating individuals as censored if they experience the competing risk event (Putter, 2007). However, in this study the length of follow means that there are no individuals lost to follow up during the twelve-month period of interest, and so any individual who has experienced the competing risk before the outcome can simply be assigned a zero value for the outcome.

### **Missing data**

Covariates that have more than 30% missing data will be excluded (an exception is made for the recent treatment variables, for which there is a particular pattern of missing data – see subsection below). Missing data on covariates with at most 30% missing data will be imputed via multiple imputation (with twenty imputations) using a regression model that uses other risk factors and the outcome variables as explanatory variables (Sterne et al., 2009). Estimates of coefficients in the final prediction rule will be combined across imputations, using standard methodology (Barnard and Rubin, 1999). It is possible that the

variable selection procedure would give different sets of variables in different imputations of the data-set; for this reason, the 'RR' method described by Wood et al. (2008) will be used. In this method, summary estimates are computed by combining information across all imputed data-sets at each stage as part of a single variable selection process. The missing indicator method will not be used even though treatment data may reasonably be regarded as missing completely at random during the period 2001-2004. In observational studies, this method has been shown empirically to bias the effect size estimates of other variables in the model even if the missing completely at random assumption holds (Groenwold et al., 2012).

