### **Recent treatment variables**

Recent treatment variables are expected to have a high proportion of missing data values because information on treatment within the preceding six months is not available for episodes dated before the beginning of 2006. For this reason, it appears reasonable to regard the missing values for these four variables as missing completely at random; in this scenario, there is evidence that multiple imputation models demonstrate good performance, and are preferable to complete-case analysis, even when the proportion of missing data is high (White and Carlin, 2010; Lee and Carlin, 2012). Therefore multiple imputation will be performed on these variables in the same way as described in the section 'Missing data'. As a sensitivity analysis, the final model (using the same set of covariate models) will be fitted using complete-case data from 2006-2008 only, and any substantial differences in point estimates noted. Standard errors of estimates in this complete-case analysis are expected to be larger owing to the smaller sample size.

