| Sibling violent crime          | 1 (3) | Binary      |                                                                                                                                                                                                                                                                                               |
| Diagnosis                      | 2     | Binary      | Classified as either 'bipolar' or 'schizophrenia' (the latter also covers the schizophrenic spectrum)                                                                                                                                                                                         |
| Recent treatment – drug class  | 2     | Categorical | Four categories (each treated as binary: 'mood', 'antipsychotic', 'antidepressant', 'dependence'); defined as any prescription collected in the six months prior to diagnosis                                                                                                                 |
| In/outpatient diagnosis        | 2     | Binary      | Indicator variable of whether patient was an inpatient or an outpatient at time of diagnosis                                                                                                                                                                                                  |
| Length of first inpatient stay | 2     | Discrete    | Measured in days, included in model as a binary variable (up to 7 days versus 8 or more days); relevant for inpatients only                                                                                                                                                                   |
| Number of episodes             | 2     | Discrete    | Includes both inpatient admissions and contacts with health services as                                                                                                                                                                                                                       |

|                                                             |       |             |                                                                                                                                                         |

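### With twenty imputations for treatment variables missing in over half of episodes, retention near p = 0.1 depends noticeably on the imputation seed

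*SAP*

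**What the plan says.** The number twenty appears once, in Missing data. There it covers covariates with at most 30% missing, which are to be "imputed via multiple imputation (with twenty imputations"). The same section sets the cap: "Covariates that have more than 30% missing data will be excluded", with the recent treatment variables exempt.

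Recent treatment variables carries the procedure over: "Therefore multiple imputation will be performed on these variables in the same way as described in the section" on missing data. The four variables are binary drug-class indicators, each "defined as any prescription collected in the six months prior to diagnosis" (Appendix 1). They belong to Group 2. Under Adjustment for risk factors they go through backward selection at p = 0.1, and Missing data specifies that estimates are pooled over all imputed data sets at each selection step.

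The period without treatment data is described in three places:
- Study Summary: "An exception is treatment history, which is available from 2005 onwards".
- Missing data: treatment data regarded as "missing completely at random during the period 2001-2004".
- Recent treatment variables: six-month information "is not available for episodes dated before the beginning of 2006".

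The SAP gives no percentage missing for these variables beyond calling it high, no reason for twenty, and no check of Monte Carlo error.

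**The concern.** Multiple imputation is random, so a pooled p-value based on a finite number of imputations varies from one run to the next on the same data. The variation grows with the share of information that is missing. Twenty was set in a sentence about covariates with at most 30% missing, then reused unchanged for variables with about twice that. Because the p-value is compared with a hard threshold, this variation can decide whether a borderline treatment variable enters the rule.

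Pooling at each selection step gives one decision per run, but it does not make that decision repeatable across runs. The 2006-2008 complete-case analysis refits the final model with the covariates already chosen, so it cannot bring back a variable dropped by chance. Four variables in two models make eight such decisions. At stake is whether another analyst following the SAP on the same data would reach the same set of predictors.

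**Working it through.** **Inputs from the SAP.** m = 20 imputations (Missing data); retention threshold 0.1 (Adjustment for risk factors); episodes "between 1st January 2001 and 31st December 2008 will be used to develop the model", i.e. 8 years (Study Summary); treatment missing before 2006 (Recent treatment variables).

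**Step 1: share missing.** With episodes even over time (an assumption), 5/8 = 62.5%. Under 2001-2004 only, 4/8 = 50%. If data began in January 2005 and a full six-month look-back were required, 4.5/8 = 56%. For a linear trend in yearly episodes, give the years weights running from 1 to r. The share before 2006 is then the sum of the first five weights over the sum of all eight:
- r = 0.5: 4.286/6 = 71%.
- r = 3: 7.857/16 = 49%.

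**Step 2: fraction of missing information (FMI).** A simulation of a binary covariate missing completely at random in a logistic model (assumed 30,000 persons, 3% outcome, outcome in the imputation model) gave FMI 0.49-0.52 at 50% missing and 0.61-0.63 at 62.5%. FMI 0.5 and 0.6 are used below.

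**Step 3: Monte Carlo error and efficiency.** Monte Carlo error as a share of the standard error is √(FMI/m):
- FMI 0.3, m = 20: √0.015 = 12.2%.
- FMI 0.6, m = 20: √0.03 = 17.3%.
- FMI 0.6, m = 60: √0.01 = 10.0%.
- FMI 0.6, m = 100: √0.006 = 7.7%.

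Relative efficiency at m = 20 is 1/(1 + 0.6/20) = 97.1%, a loss of about 3%.

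**Step 4: the decision at 0.1.** Call the p-value with unlimited imputations on the same data the exact p, with z its normal deviate. Scale the total variance to 1, so that B = FMI and W = 1 − FMI. Over runs:
- pooled estimate ~ N(z, B/m);
- between-imputation variance b ~ B·χ²(m−1)/(m−1);
- T = W + (1 + 1/m)b;
- p from a t distribution with (m−1)/λ² degrees of freedom, where λ = (1 + 1/m)b/T.

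If a proportion k of runs retains the variable, two seeds disagree with probability 2k(1−k).

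| FMI | Exact p | Dropped, m = 20 | m = 60 | m = 100 | Two seeds disagree, m = 20 | m = 60 | m = 100 |
|---|---|---|---|---|---|---|---|
| 0.6 | 0.01 | <0.1% | 0% | 0% | 0.1% | 0% | 0% |
| 0.6 | 0.03 | 3% | <0.1% | <0.1% | 6% | <0.1% | <0.1% |
| 0.6 | 0.046 | 10.7% | 0.8% | <0.1% | 19% | 1.5% | 0.1% |
| 0.6 | 0.10 | 57% | 54% | 53% | 49% | 50% | 50% |
| 0.6 | 0.15 | 85% | 95% | 98% | 26% | 10% | 4% |
| 0.6 | 0.20 | 96% | 99.8% | 100% | 8% | 0.5% | <0.1% |
| 0.6 | 0.30 | 99.8% | 100% | 100% | 0.5% | 0% | 0% |
| 0.5 | 0.046 | 7% | 0.3% | <0.1% | 13% | 0.5% | <0.1% |

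For the exact p = 0.046 row: 2 × 0.107 × 0.893 = 19%. At FMI 0.6 and exact p = 0.10, the pooled p falls between about 0.035 and 0.23 in 95% of runs with m = 20, and between 0.064 and 0.15 with m = 100.

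**Step 5: averaged over data sets.** Letting z vary as N(μ, 1) at FMI 0.6, the chance per variable that two seeds disagree is:
- μ = 0: about 5% with m = 20, 2% with m = 100.
- μ = 1.645: 11% and 5%.
- μ = 4: 1% and 0.3%.

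**The case against.** The strongest reply is that twenty imputations add little to the instability that p-value selection already has. With sampling variation included, at FMI 0.6, a variable with expected z = 2.0 is dropped in 38.2% of data sets with 20 imputations, 36.5% with 100 and 36.2% with unlimited imputations. Step 4 therefore measures repeatability on one fixed data set, not how often selection reaches the right answer. The SAP also describes Group 2 variables as likely to be associated with the outcomes, and nothing in it places any treatment variable near 0.1. The main output is a predicted probability, and no effect on discrimination or calibration has been shown. All of this stands, and it limits the point to borderline variables.

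A reader might infer that retention depends on the seed in general, or that the imputed estimates are unsound. Neither follows: at exact p of 0.01 or 0.30 two seeds disagree at most about 0.5% of the time, and the efficiency loss is about 3%.

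A reader might also infer from the differing dates that 2005 episodes with a truncated look-back would be coded as untreated. The SAP does not support that. The section on recent treatment variables governs them, treats every episode before 2006 as missing, and matches the 2006-2008 complete-case set. The mention of 2001-2004 is an aside in the argument against the missing-indicator method. Only loose wording remains.

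**Conclusion.** The point holds in a limited form. Twenty imputations are adequate for estimation but thin for a repeatable keep-or-drop decision on a treatment variable whose exact p lies at roughly 0.03-0.20. A variable at exactly 0.10 stays close to a coin flip whatever the number of imputations, so raising it narrows the unstable zone without removing it. Averaged over data sets, two seeds disagree for roughly 1-11% of treatment variables with 20 imputations, against 0.3-5% with 100.

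These figures assume FMI close to the share missing, the normal and chi-square approximations of Rubin's rules, and a single decision at 0.1 rather than the full backward sequence. The share missing is inferred from dates, since the SAP gives none. The conclusion survives its lower end: at FMI 0.5 the drop rate for exact p = 0.046 is still 7%. This is a worthwhile, cheap improvement and not a flaw that threatens the model.

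**What to change.** In Missing data, replace twenty with about 100 imputations (at least 60), and say that this applies to the recent treatment variables too. Fix the seed in advance and record it. Report the Monte Carlo error of any treatment p-value close to 0.1. Do not promise to add imputations until the decision is stable, because a variable at exactly 0.10 would never settle. The cost is computing time, about five times the imputation and pooled-selection work (100/20), or three times with 60.

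As a wording correction only, align the reference to 2001-2004 in Missing data and to availability from 2005 in Study Summary with the operative rule in Recent treatment variables: the six-month treatment variables are missing for every episode before 2006. This costs a sentence or two.
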